### Economic evaluation

A cost-utility analysis (CUA) from a societal perspective will be undertaken using patient level data collected alongside the clinical trial. A CUA compares the incremental costs and benefits, expressed in Quality Adjusted Life Years (QALYs) gained, of alternative programs. Costs will include direct costs (e.g. intervention cost) as well as indirect costs (e.g. lost productivity). Costs will be obtained by valuing the resources consumed using unit prices from standard costing resources such as the Medicare Benefits Schedule and relevant award wages in Australia. QALYs gained will be estimated, which is a measure of a person’s life expectancy, weighted by their utility score measured using the Assessment of Quality of Life – 8 dimensions (AQoL-8D) multi-attribute utility instrument at baseline, immediately following the supervised phase, and at 3, 6 and 12 months [111]. The incremental cost-effectiveness ratio (ICER) will be calculated, which is the difference in mean costs divided by the difference in mean QALYs. Sensitivity analysis will be conducted to assess the impact of input parameters (e.g. costs) on the results, and non-parametric bootstrapping will be used to characterise uncertainty around the ICER. In addition, sub-group cost-effectiveness analysis will be performed to explore heterogeneity of results between patients’ subgroups.

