### Randomisation

Following completion of the 4-week supervised training phase and the second testing session, participants will be stratified by sex and age before being randomly assigned (1:1 allocation ratio) to either a peer support group or a non-peer support group. Randomisation will be performed using a computerised random number generator by a research officer independent to the study. Non-systematic block sizes of four, six, or eight will be used to ensure allocation concealment. Randomisation history will be kept secure by the independent research officer in an electronic password-protected file. The independent research officer will confidentially communicate the allocation result to the trial’s primary investigator within 48 h after completing outcome testing following the second testing session. All investigators will be blinded to group allocation for baseline testing, the supervised phase and for testing following the supervised phase, with randomisation occurring after the completion of testing following the supervised phase. The primary outcome will be analysed by a researcher blinded to group allocation. Unblinding will not be permissible under any circumstances. A schematic representation of the study protocol is shown in Fig. 1.

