### 4-week supervised high intensity interval training phase

Following familiarisation with the procedures, participants will complete 12 HIIT sessions over 4 weeks, supervised by an AEP. Training sessions will be conducted at the School of Human Movement and Nutrition Sciences, The University of Queensland, and be performed in small groups of less than five participants. Prior to exercising, participants’ heart rate and blood pressure will be measured to indicate any contraindications to commencing exercise as outlined by the American College of Sports Medicine [43]. Each training session will follow the procedure as previously described by Devin et al. [19] (see Fig. 2).

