### Statistical considerations and data analysis

A priori power calculations determined that a sample of *n* = 188 (*n* = 94 per group) will be needed to detect a minimum between-group difference in MVPA levels at 12 months, with 80% power and 5% alpha. To account for an anticipated dropout rate of 20%, 226 participants (*n* = 113 per group) will thus be recruited for this study. A priori criteria for successful provision of peer support will be contacting participants on average on one or more occasions per week over the 12-month maintenance phase.

Data will be assessed for normality of distribution using the Kolmogorov-Smirnov test. Raw continuous data (e.g. minutes of MVPA per day) will be analysed using linear mixed (fixed and random) modeling, to assess changes over time and differences between groups. Group, time, and group × time interaction will be treated as fixed factors; participants will be treated as a random factor with individual intercepts. Each model will include covariates, as appropriate, and will be adjusted using the baseline value as a fixed continuous covariate as previously described by Courneya et al. [113]. Model residuals will be formally assessed for normality by use of the Kolmogorov-Smirnov test and visual inspection of histogram plots. Bonferroni pairwise adjustments will be made for all subsequent comparisons.

Non-continuous data will be analysed with the target distribution and relationship fixed to multinomial logistic regression. Statistical significance will be set at an alpha of *p* < .05 and analyses will be conducted using the intention-to-treat approach. There are no interim analyses planned or early trial termination guidelines. Data from the peer supporters will be analysed separately to those of the participants.

Qualitative data from the semi-structured interview transcripts will be assessed using inductive thematic analysis. Codes will be assigned to salient text segments across the entire data set, before codes will be combined to define overarching themes [108].

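### The incremental QALY is given without adjustment for utility at randomisation or a stated start at randomisation; fixing both is a free gain in precision for a tertiary analysis

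*Protocol article*

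**What the plan says.** The Economic evaluation section of the protocol article plans a cost-utility analysis on patient-level data. It explains the ICER as a ratio, "which is the difference in mean costs divided by the difference in mean QALYs", and names no covariate for either part. QALYs are weighted by AQoL-8D utility measured "at baseline, immediately following the supervised phase, and at 3, 6 and 12 months". Uncertainty is to be shown by non-parametric bootstrapping.

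The Randomisation section sets the order of events: "Following completion of the 4-week supervised training phase and the second testing session, participants will be stratified by sex and age before being randomly assigned". Two of the five listed utilities are therefore measured before allocation: one about 4 weeks earlier, the other at the visit that immediately precedes it. Utility is not a stratification factor.

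The Statistical considerations section says of the linear mixed models that each "will be adjusted using the baseline value as a fixed continuous covariate". The economic section has no matching statement. Table 1 lists the economic evaluation among the tertiary outcomes and schedules the AQoL-8D at the post-supervised-phase visit.

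**The concern.** A QALY total over 12 months contains the utility at randomisation directly and depends on it indirectly, because people who start with high utility tend to keep it. If the arms differ by chance in utility at randomisation, a simple difference in mean QALYs carries most of that gap with it. Regression on the starting utility removes this component and narrows the interval.

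The adjustment planned for the clinical models does not plainly reach the QALY, which is one total per person and not a repeated measure. If that adjustment were carried over, the word baseline would point to the visit before the supervised phase and not to the visit at randomisation.

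A series of utilities that begins before the supervised phase could also be integrated from its first point. That would count 4 weeks in which both arms were treated alike.

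At stake are the precision of the incremental QALY and the spread of the bootstrap replicates around the ICER.

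**Working it through.** The document gives no QALY difference, utility SD or ICER, so there is no figure of the plan's own to reproduce. What follows is an illustration.

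**Inputs from the article**
- 94 per group with data (Statistical considerations).
- Utilities at randomisation (post-supervised-phase visit), 3, 6 and 12 months (Economic evaluation, Table 1).
- Supervised phase of 4 weeks: 4/52 = 0.077 year.

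**Assumptions not in the article**
- QALYs are the trapezoidal area under the utility curve.
- Utility SD is 0.15 to 0.20.
- One equal correlation ρ holds between all visits, from 0.5 to 0.8.

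**Weights.** The intervals are 0.25, 0.25 and 0.5 year. The weights on the four utilities are 0.125, 0.25, 0.375 and 0.25. They sum to 1, and their squares sum to 0.28125.

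**Formulas**, in units of the utility variance
- Variance of one person's QALY: V = ρ + (1 − ρ) × 0.28125.
- Slope of the QALY on utility at randomisation: b = 0.125 + 0.875ρ.
- Variance after adjustment: V − b².
- SE of the arm difference: SD × √(variance × 2/94).

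| ρ | V | b | V − b² | SE ratio, adjusted to unadjusted |
|---|---|---|---|---|
| 0.5 | 0.6406 | 0.5625 | 0.3242 | 0.71 |
| 0.6 | 0.7125 | 0.6500 | 0.2900 | 0.64 |
| 0.7 | 0.7844 | 0.7375 | 0.2405 | 0.55 |
| 0.8 | 0.8562 | 0.8250 | 0.1756 | 0.45 |

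The reduction in SE runs from 29% (ρ = 0.5) to 55% (ρ = 0.8). It does not depend on the SD.

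**Worked case**, SD 0.20 and ρ = 0.6
- Unadjusted: √(0.7125 × 0.04 × 2/94) = 0.0246.
- Adjusted for utility at randomisation: √(0.2900 × 0.04 × 2/94) = 0.0157.
- Adjusted instead for utility at the pre-supervised-phase visit, under the same equal-correlation model: 0.0173. The choice of visit matters, but less than adjusting at all.

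**Chance imbalance.** The SE of the arm difference in utility at randomisation is SD × √(2/94): 0.022 at SD 0.15 and 0.029 at SD 0.20. A one-SE imbalance moves the unadjusted QALY difference by b times that amount: 0.0219 × 0.5625 = 0.012 to 0.0292 × 0.825 = 0.024 QALYs.

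**Pre-randomisation interval.** Including the 4 weeks adds 0.038 to the weight of each of the first two utilities. In the worked case the unadjusted SE rises from 0.0246 to 0.0263, about 7%. The expected arm difference over that interval is zero.

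**If correlation decays.** Suppose the correlation is ρ per 3 months, so that with ρ = 0.8 utility at randomisation correlates 0.80, 0.64 and 0.41 with the utilities at 3, 6 and 12 months. Then b = 0.125 + 0.25 × 0.80 + 0.375 × 0.64 + 0.25 × 0.41 = 0.667. V is 0.751, V − b² is 0.305 and the SE ratio is √(0.305/0.751) = 0.64. The reduction is 36% in place of 55%. The same decay with ρ = 0.5 gives V = 0.496, b = 0.359 and a ratio of 0.86, a reduction of 14%.

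**The case against.** The strongest reply is that the section does not call the means raw. The phrase about means is the usual definition of an ICER and fits regression-adjusted means as well. A reader might infer that the plan has chosen an unadjusted analysis, but the text does not support that. It is silent, and an article often leaves such detail to a fuller plan.

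A reader might likewise infer that QALYs are counted from the pre-supervised-phase visit. The list of visits says when utility is measured. The outcome section on the AQoL-8D gives the same schedule for the instrument alone, and no sentence states when the QALY window opens. The post-supervised-phase value is exactly what a start at randomisation needs.

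It is also tempting to call the unadjusted difference biased. Under randomisation it is not. Chance imbalance is part of its sampling error, which the bootstrap reflects.

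Nor does the Discussion rest national adoption on the ICER. It speaks conditionally, and the effect on MVPA is central to what it says.

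All of this stands and limits the point. What remains is that the section names an estimator and a utility series. Followed as written, they give a valid but less precise answer than the collected data allow.

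**Conclusion.** The point holds as a free improvement to a tertiary analysis. It is not an error that invalidates the result. The section names no adjustment for utility and does not fix the QALY start at randomisation. A literal analysis would be unbiased but imprecise, and any chance imbalance in utility would show in the realised ICER.

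Under equal correlations of 0.5 to 0.8, adjustment cuts the SE of the QALY difference by about 29% to 55%. Under the decaying pattern shown, the cut is 14% to 36%. These figures rest on assumed correlations, and the absolute SEs also on an assumed SD; neither is in the article. The pre-randomisation interval is the minor part: about 7% on the unadjusted SE in the worked case, with no expected difference between arms.

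**What to change.** State three things in the Economic evaluation section or the health economics plan:

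1. QALYs accrue from the post-supervised-phase visit, taken as randomisation, to 12 months.
2. The incremental QALY is the arm coefficient from a regression of QALYs on arm, AQoL-8D utility at that visit, and the randomisation strata (sex and age).
3. Costs and adjusted QALYs are bootstrapped jointly: participants are resampled with their cost and QALY kept together, and the regression is refitted in each replicate.

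Do not simply apply the QALY start date to costs. The section on recruitment and training of peer supporters has them complete a training course of one or two days and their own supervised HIIT phase. These resources belong to the peer-support arm alone and may be used before a given participant is randomised. All costs specific to that arm should stay in the numerator, or the ICER would flatter peer support.

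The change costs a few sentences. The utility is already scheduled at the required visit, so no new data are needed. Fixing the rule before the data are seen also removes any later choice between adjusted and unadjusted ICERs.

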### Ethics and dissemination

This study has institutional ethical approval through the Human Research Ethics Committee of Bellberry Ltd. (#2015–12-840). Any future amendments to the protocol and/or associated documents will be submitted for approval through Bellberry Ltd.

Outcomes of this trial will be published in international, high-quality, peer-reviewed journals, and the findings will be presented at national and international conferences and meetings. Findings will also be communicated at community and consumer-led forums and will be presented at local hospital departments and university seminars.

## Discussion

The aim of the proposed trial is to determine the influence of peer support, compared to no peer support, on MVPA and various markers of health 12 months following a brief supervised exercise intervention in cancer survivors. If peer support significantly improves maintenance of MVPA compared to no peer support, it will emerge as a potentially sustainable and feasible means of enhancing cancer survivor’s engagement in physical activity following completion of a supervised exercise intervention. Further, should peer support also be shown to enhance the maintenance of physiological and psychosocial outcomes such as cardiorespiratory fitness, body composition and quality of life compared to no peer support, the long-term health and wellbeing of people living with and beyond cancer would be significantly improved. The economic evaluation will also provide evidence of the cost-effectiveness of peer support to maintain PA following a supervised exercise intervention.

Should peer support be shown to be (cost-) effective strategy to maintain MVPA following a supervised exercise intervention, it can potentially be adopted and implemented at a national level through existing peer support infrastructures of the State and Territory Cancer Councils, the primary providers of post-treatment support of cancer patients in Australia. A peer support-exercise model has the long-term potential to reduce comorbidities, improve physical and mental wellbeing, and significantly reduce the burden of disease in cancer survivors.

## Data Availability

Not applicable.

## Abbreviations

$$ \dot{\mathrm{V}}{\mathrm{O}}_{2\mathrm{peak}} $$: Peak volume of oxygen consumption
AEP: Accredited Exercise Physiologist
AQoL-8D: Assessment of Quality of Life – 8 dimensions multi-attribute utility instrument
BMI: Body mass index
BSI: Brief Symptom Inventory
CCQ: Cancer Council Queensland
CRP: C-reactive protein
CUA: Cost utility analysis
DASS: Depression Anxiety Stress Scale
DXA: Dual energy x-ray absorptiometry
ELISAs: Enzyme-linked immunosorbent assays
EORTC QLQ-C30: European Organization for Research and Treatment of Cancer quality of life questionnaire for people with cancer
FACIT-F: The Functional Assessment of Chronic Illness Therapy: Fatigue
FACT-G: Functional Assessment of Cancer Therapy: General
GAD-7: Generalised Anxiety Disorder 7-item scale
GCP: Good Clinical Practice
HIIT: High intensity interval training
HR: Heart rate
HR_peak_: Peak heart rate
ICER: Incremental cost-effectiveness ratio
IGF: Insulin-like growth factor
IGFBP: Insulin-like growth factor binding protein
IL: Interleukin
ISAK: International Society for the Advancement of Kinathropometry
ISI: Insomnia Severity Index
MVPA: Moderate-to-vigorous physical activity
NHMRC: National Health and Medical Research Council
PA: Physical activity
PHQ-9: Patient Health Questionnaire-9
QALYs: Quality-adjusted life-years
RCT: Randomised controlled trial
SF-36: Short form 36 health survey
TNF-α: Tumour necrosis factor – alpha
WAI: Working Alliance Inventory
